**Figure 1 fig1:**
[figure not shown]
Study flow and haemostatic assessments in trial. Critically ill patients receiving UFH or LMWH are screened and enrolled consecutively. Two blood samples are obtained per patient: the first at study inclusion and the second 24–72 h later. For LMWH, sampling targets peak plasma concentration at 4 h after subcutaneous administration. For continuous UFH infusion, sampling is performed at steady state, defined as ≥6 h after initiation or ≥4–6 h after dose adjustment. Laboratory analyses include viscoelastic testing (ClotPro® RVV, EX, ECA, RVH ± IN/HI), chromogenic Anti-Xa activity (UFH/LMWH), standard laboratory assays (aPTT, INR, antithrombin, fibrinogen, platelet count, D-dimers), and advanced haemostatic markers (factor VIII, factor XIII, PF1 + 2, TGA, PAP, PAI, TFPI, TAT). All assays are derived from the same sampling time point. Plasma samples for thrombin generation and ELISA-based assays are processed immediately, aliquoted, and stored at −80 °C. These measurements are performed in batch analysis to minimise inter-assay variability. aPTT, activated partial thromboplastin time; ECA, ecarin test; INR, international normalized ratio; LMWH, low-molecular-weight heparin; PAP, plasmin-antiplasmin complexes; PAI, plasminogen activator inhibitor; RVV, Russell’s viper venom test; TGA, thrombin generation assay; TAT, thrombin-antithrombin complexes; TFPI, tissue factor pathway inhibitor; UFH, unfractionated heparin; VET, viscoelastic testing.

### Study population and recruitment

2.3

Participant selection is based on predefined inclusion criteria and is conducted entirely on a voluntary basis, with informed consent obtained before participation. Given the biological and clinical heterogeneity inherent to critically ill ICU patients, sufficient sample size is required to allow modelling of patient-level variability and pre-specified effect modification.

Inclusion criteria for critically ill patients are as follows:

≥18 yearsUndergoing anticoagulation therapy with UFH, LMWH at any dosageWritten informed consent by patient or legal representative

The following variables are recorded to enable further classification:

Sepsis or septic shock within the last 48 h according to the SEPSIS-3 criteria (33) using the SOFA score, continuously collected hemodynamic variables and results of blood gas analysis

Exclusion criteria:

Known hereditary coagulation disorderPatients receiving ongoing therapeutic oral anticoagulants (direct oral anticoagulants or vitamin K antagonists) will be excluded from the primary analysis. Patients with prior exposure may be included only if clinically relevant residual drug activity can be excluded based on documented timing and renal function.

All ICU patients treated with UFH or LMWH will be screened, and eligible patients will be consecutively enrolled until the target sample size is reached. Enrolment will be based on fulfilment of the inclusion criteria and will proceed only after fully voluntary informed consent has been obtained. Sepsis status will be defined according to Sepsis-3 criteria (33). SOFA score will be recorded as a continuous variable and additionally explored as a predefined severity modifier (e.g., SOFA ≥ 9) within effect-modification analyses.

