### Viscoelastic testing

2.7

Viscoelastic testing will be performed immediately on the ICU using the ClotPro® device. Testing will follow manufacturer-specific standard operating procedures. After electronic patient identification entry, the corresponding test channel and cartridge will be selected. Test-specific pipette tips will be scanned, and citrated whole blood will be transferred into the test cup, gently mixed, and the measurement initiated.

The following assays will be performed according to anticoagulant type:

LMWH / UFH: EX-, RVV-, RVH-, ECA-test.UFH: additional IN/HI-test.

Recorded parameters include CT, CFT, A5, A10, MCF, lysis time (LT), maximum lysis (ML), and alpha angle. Time from sampling to test initiation will be documented. After test completion, measurement channels will be prepared according to hygiene standards. Residual blood will be discarded in designated biohazard containers. The POC devices used in this study, which are operated outside the central laboratory, undergo weekly quality control in accordance with the manufacturer’s specifications.

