
Specialized haemostasis markers are included to mechanistically characterise discordant profiles between concentration-based heparin activity (Anti-Xa) and functional assays (VET/TGA): PF1 + 2 and TAT as thrombin generation/consumption markers; TFPI as a heparin-responsive anticoagulant pathway marker; PAP and PAI-1 as fibrinolysis activity/inhibition markers. These variables will be analysed descriptively and in focused secondary models to reduce data-driven inference. Table 1 provides an overview about the obtained data.

**Table 1 tab1:** Collected study variables.

Grouping	Variables
Demographic data	Date of ICU admission; Admission diagnosis; Main diagnosis; Gender; Date of birth; Age; Height; Weight; Date of blood collection
Comorbidities	Trauma; Injury Severity Score; Diabetes; Obesity; Coronary heart disease; Chronic arrhythmia; COPD; Other lung diseases; Venous thrombosis; Nicotine abuse; Active tumour disease; Chronic renal insufficiency; Chronic dialysis; Bleeding disorder upon admission; Thromboembolic complication upon admission; Ischemic stroke; Haemorrhagic stroke; Nosocomial infection; Liver diseases
Condition at time of blood collection	Ventilation status; Glasgow Coma Scale; SpO₂; PaO₂; FiO₂; Systolic blood pressure; Diastolic blood pressure; Mean arterial pressure; Heart rate; Catecholamine use and dosage; Inotrope use and dosage; Temperature; Spontaneous respiratory rate; ECMO status; Date of ECMO initiation
Complications within last 24 h	Bleeding (date, volume, transfusion requirements: RBC, FFP, platelets, PPSB, other blood products); Thrombosis; Pulmonary embolism
Severity scores	SOFA; SAPS II
Medication	Sedation and dosage; Platelet aggregation inhibition and dosage; Oral anticoagulation (drug, dosage, time of last intake); Other anticoagulants and dosage; UFH dosage; LMWH dosage and drug name; Parenteral nutrition; Immunosuppressants
Viscoelastic testing (ClotPro®)	LMWH: EX, RVV, ECA, RVH; UFH: EX, RVV, ECA, RVH, IN, HI; Recorded variables: CT, CFT, A5, A10, MCF, Lysis time, Alpha angle
Standard laboratory tests (SLT)	Haemoglobin; Hematocrit; Platelet count; Leukocytes; Prothrombin time (Quick); aPTT; Anti-Xa; dTT; Antithrombin; D-dimer; Fibrinogen; Calcium; Factor VIII; Factor XIII; C-reactive protein; Procalcitonin; Creatinine; Glomerular filtration rate; Urea; ALAT; ASAT; Bilirubin; Albumin; Triglycerides
Advanced haemostatic assays	TAT; PF1 + 2; TGA; PAP; PAI; TFPI

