
Sepsis, multi-organ failure, and endothelial dysfunction alter pharmacokinetics and pharmacodynamics, complicating both drug absorption and elimination. Consequently, Anti-Xa monitoring provides only a concentration-based readout and does not reflect the complex interplay between the procoagulant and anticoagulant pathways. In particular, it neglects the influence of elevated fibrinogen levels due to inflammation, increased platelet activation, and impaired fibrinolytic activity. Similarly, standard laboratory tests such as aPTT and INR are confounded by acute-phase reactants and inflammatory mediators. Additionally, Anti-Xa activity reflects heparin-dependent inhibition of a fixed amount of exogenous factor Xa and is therefore largely independent of endogenous factor X levels. In contrast, CT-RVV in whole blood may be influenced by variations in coagulation factor concentrations, including factors V and X. Such variability is considered part of the biological context of critical illness and is not treated as methodological noise but as a potential modifier of assay concordance. As a result, neither Anti-Xa nor conventional coagulation tests adequately capture the dynamic risk of bleeding and thrombosis in critically ill patients.

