Point-of-care tests such as VET provide the practical advantage of immediate bedside results, potentially enabling timely adjustment of therapy. As has already been shown, VET can complement the monitoring of argatroban therapy and, in certain situations, may serve as the sole method, providing better performance than aPTT but without exceeding the accuracy of dTT (37). However, robust evidence on whether VET can substitute for or complement Anti-Xa monitoring in UFH and LMWH administration in critically ill patients is still lacking. Consequently, the clinical utility of these assays remains uncertain, particularly in sepsis and at prophylactic LMWH dosing, where therapeutic failure is frequently observed. The present study addresses these gaps by prospectively measuring Anti-Xa, VET, TGA, and extended haemostatic markers in critically ill patients treated with UFH or LMWH. By systematically evaluating correlations, dose–response relationships, and patient-specific modifiers, the trial aims to clarify whether VET clotting times in the RVV test can serve as surrogates for Anti-Xa. In addition, secondary analyses will assess whether VET or Anti-Xa aligns more closely with global haemostatic function, as defined by TGA variables, and whether TGA can help explain discordant results between concentration-based monitoring and functional assays. Ultimately, the results are expected to define the potential and limits of bedside viscoelastic monitoring and to guide patient-tailored anticoagulation strategies aimed at reducing both thrombotic and bleeding complications.

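### The exclusion of non-heparin anticoagulants covers only ongoing therapeutic oral agents, and prior exposure is cleared on timing and renal function, so other drug effects can enter the primary CT-RVV/Anti-Xa analysis

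*Protocol article*

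**What the plan says.** Section 2.3 admits adults on UFH or LMWH at any dose. It does not require heparin to be the only anticoagulant. The relevant exclusion covers oral agents (direct oral anticoagulants and vitamin K antagonists) that are both ongoing and therapeutic, and it applies to the primary analysis. Earlier exposure is handled by one sentence: "Patients with prior exposure may be included only if clinically relevant residual drug activity can be excluded based on documented timing and renal function".

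Other places bear on this rule:

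- Table 1 (section 2.10) lists under medication "Oral anticoagulation (drug, dosage, time of last intake); Other anticoagulants and dosage", and among the standard laboratory tests "aPTT; Anti-Xa; dTT; Antithrombin".
- Section 2.7 assigns these viscoelastic tests to every patient: "LMWH / UFH: EX-, RVV-, RVH-, ECA-test". Section 2.2 describes RVH as the Russell viper venom test with heparinase. Section 2.6 includes Quick/INR.
- The Discussion says that "CT-RVV in whole blood may be influenced by variations in coagulation factor concentrations, including factors V and X", whereas Anti-Xa is largely independent of endogenous factor X. It also says that "VET can complement the monitoring of argatroban therapy".
- The primary model (section 2.13.1) relates CT-RVV to Anti-Xa with a random patient intercept and a fixed effect for UFH versus LMWH. The modifiers in section 2.13.2 are sepsis, antithrombin, renal function and inflammatory markers.
- The analysis population (sections 2.15 and 4.7) needs only one valid pair of measurements.

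**The concern.** The primary question is whether CT-RVV follows heparin activity, as measured by Anti-Xa, stably enough to be read as a surrogate, and under which conditions that relation worsens. A second anticoagulant in the sample disturbs this in one of two ways. If it raises both readings, part of the estimated association is not due to heparin. If it prolongs CT alone, it adds discordance that has nothing to do with heparin or critical illness but appears in the same data in which section 2.13.2 looks for clinical modifiers.

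The rule leaves two openings. First, the evidence it names for clearing prior exposure suits drugs that leave the body with time and through the kidney. A vitamin K antagonist acts by lowering clotting factors, and renal function says little about how far these have recovered. Second, the words ongoing, therapeutic and oral each narrow the exclusion. A patient who receives UFH or LMWH together with, or soon after, a parenteral non-heparin agent meets every stated criterion. So does one on a low-dose oral agent.

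**Working it through.** **Text check.** No figure in the plan depends on this rule, so there is none to reproduce. The passages compare as follows.

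1. *Prior vitamin K antagonist.* The class is named in the exclusion. The clearance evidence is timing and renal function; INR is measured but not used for this. By the article's own account, factor X can move CT-RVV while leaving Anti-Xa largely alone. That vitamin K antagonists lower factor X is general pharmacology and is not stated in the article.
2. *Non-oral and low-dose oral agents.* These are recorded (Table 1) but not excluded. The prior-exposure sentence follows the one on oral agents and does not clearly reach parenteral ones.
3. *Later safeguards.* The primary model, the modifiers and the analysis population contain no condition or term for other anticoagulants. RVH and ECA are run in everyone and dTT is listed, but none is tied to eligibility or to removal of a pair.

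**Illustration of size.** Inputs from section 2.12: 66 patients (30 LMWH, 36 UFH), two samples each, ICC 0.3. Assumed: true correlation 0.4, with both assays in SD units; share of affected patients f = 5% or 10%; a shift that is constant within the patient and unrelated to heparin level, either +1.5 SD on both assays or +2 SD on CT only.

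For a simple pooled regression of CT on Anti-Xa, with shifts dx (Anti-Xa) and dy (CT):

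slope = [r + f(1−f)·dx·dy] / [1 + f(1−f)·dx²]

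- Both +1.5 SD, f = 5%: (0.4 + 0.0475 × 2.25) / (1 + 0.0475 × 2.25) = 0.507 / 1.107 = 0.46
- Both +1.5 SD, f = 10%: (0.4 + 0.09 × 2.25) / (1 + 0.09 × 2.25) = 0.6025 / 1.2025 = 0.50
- CT only (dx = 0), any f: 0.4 / 1 = 0.40

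The planned mixed model also uses within-patient contrasts, in which a constant patient-level shift cancels, so its slope moves less. Simulation of the random-intercept model gave the following; the ranges reflect small differences in set-up between runs.

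| Setting | Mixed-model slope | Spearman |
|---|---|---|
| No contamination | 0.40 | 0.38 |
| Both assays +1.5 SD, 5% | 0.44–0.45 | 0.42 |
| Both assays +1.5 SD, 10% | 0.47–0.48 | 0.47 |
| CT only +2 SD, 5% | 0.40 | 0.36 |
| CT only +2 SD, 10% | 0.40 | 0.34 |

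The standard error of the slope is about 0.08 without contamination. A CT-only shift in 10% of patients raises it from about 0.083 to 0.092. For the shift on both assays, the change at 5% is about half a standard error (0.04 / 0.08). At 10% it is about 0.9 of one (0.075 / 0.08).

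With the planning value r = 0.669 and +2 SD shifts, independent pairs show the same pattern. A shift on both assays moves Spearman from 0.65 to 0.69 (5%) and 0.72 (10%). A CT-only shift moves it to 0.61 and 0.58, with the slope unchanged.

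**The case against.** The strongest reply is that section 2.3 already sets the right requirement: a previously exposed patient comes in only if clinically relevant residual activity can be excluded. Timing and renal function are the evidence for that requirement and do not replace it. A shift of 1.5 to 2 SD would be clinically relevant, so a share of 10% after such a screen has no support in the document. This stands. A reader might infer that residual drug effect does enter the primary association, and the text does not support that. It shows only that such effect can enter, most plainly through agents that the rule does not cover.

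A reader might also infer that the primary estimate is biased in either direction, depending on the drug. That does not hold for the planned analysis. Sections 2.13.1 and 2.14 make the mixed-model slope the primary inference and the Spearman coefficient descriptive. A CT-only effect unrelated to Anti-Xa leaves the slope where it was. It would move the slope only if exposed patients also tended to have higher or lower Anti-Xa, on which the document is silent.

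Two further points have weight. Hard INR or RVH cut-offs would be a poor remedy: the Discussion treats variation in clotting factors as part of the biology under study and calls INR confounded in these patients, and RVH clotting time is closely related to the outcome. Also, drug-specific intervals or a sensitivity analysis may sit in the full protocol or the analysis plan. Their absence from the article is not criticised here; the criticism is of the scope and evidence that the article does state.

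Some of the mechanism is outside the document. That a non-heparin Xa inhibitor raises a heparin Anti-Xa reading is an assumption of the illustration. The argatroban remark concerns viscoelastic testing in general and does not show that CT-RVV responds.

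**Conclusion.** The point holds as a gap in the stated rule. The exclusion is too narrow for a primary analysis meant to isolate heparin effect, and the named clearance evidence does not fit vitamin K antagonists. The consequence is a possible upward bias in the slope from agents that raise both assays: from about 0.40 to about 0.45 at 5% contamination and about 0.47 at 10%, on an assumed +1.5 SD shift. For agents that affect CT alone, the slope keeps its value but is less precise, the descriptive correlation is lower, and there is added apparent discordance. All of this rests on assumed shares and shifts, and at low shares the effect is within sampling error. A claim that such discordance will be reported as an effect of sepsis would go too far; the plan merely offers no stated way to tell the two apart. In a study that calls itself primarily hypothesis-generating this is a modest weakness, but cheap to remove.

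**What to change.** 1. Widen the section 2.3 exclusion from the primary analysis to any concurrent non-heparin anticoagulant, oral or parenteral, at any dose.
2. Apply the residual-activity condition to prior exposure to any such agent. Use results already collected (INR, ECA, RVH, and dTT where measured) as supporting evidence next to timing and renal function, not as stand-alone cut-offs. The qualifier on dTT is needed because it appears in Table 1 but not in the section 2.6 list or the Figure 1 legend.
3. Add one sensitivity analysis: repeat the primary mixed model without all previously or concurrently exposed patients, identified from the recorded medication data, and report the slope and its confidence interval beside the primary result.

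The cost is an amended criterion and one extra model run. A few patients may be lost from the primary analysis. No new assay is needed, provided dTT is used only where it is measured anyway.

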### Setting and intervention

2.4

The study will be conducted at the Department of Anaesthesiology and Intensive Care Medicine, University Hospital Carl Gustav Carus, Technische Universität Dresden, Germany. The department provides tertiary care for critically ill patients and includes multiple specialized intensive care units with a broad spectrum of medical and surgical cases. All laboratory analyses, including point-of-care VET ClotPro® and conventional laboratory assays, will be performed within the hospital’s accredited clinical laboratories. Data collection and storage will take place within the secure institutional network of the University Hospital Dresden.

### Laboratory procedures and pre-analytical handling

2.5

Blood will be drawn from an arterial line using a standardized discard volume. For VET, citrated whole blood (3.2% sodium citrate) will be analysed on ClotPro® immediately after gentle inversion and within 120 min of sampling under controlled temperature conditions as per manufacturer instructions. For plasma-based assays (Anti-Xa, TGA, SLTs, and specialized markers), samples will be collected in 3.2% citrate tubes and processed within 60 min. Plasma preparation will be performed in a designated laboratory area using pre-programmed centrifugation settings. After centrifugation, supernatant plasma will be aliquoted into polypropylene tubes (300 μL per aliquot) and temporarily stored at −80 °C storage for batch analysis. This procedure ensures minimisation of platelet contamination and stabilisation of labile coagulation markers (e.g., PF1 + 2, TAT, TGA parameters).

### Standard laboratory tests

2.6

Conventional laboratory samples will be transported to the central laboratory. The following assays will be performed: Quick/INR, aPTT, Anti-Xa activity, Antithrombin, D-dimers, fibrinogen, factor VIII (UFH patients only), factor XIII, platelet count, and routine biochemistry (creatinine, urea, estimated GFR, ASAT, ALAT, bilirubin, triglycerides, albumin). Anti-Xa activity will be measured using a chromogenic assay (platform and reagent specified in the final manuscript), with no exogenous antithrombin is added. Antithrombin concentration will be recorded concomitantly. Routine biochemistry and inflammatory markers (CRP, procalcitonin) will only be re-measured if the last determination exceeds 24 h; otherwise, values from the daily clinical laboratory will be used. Routine coagulation parameters (Quick/INR, aPTT, fibrinogen, D-dimers) and Anti-Xa activity will be measured using a STAGO coagulation platform (Diagnostica Stago, France). The chromogenic Anti-Xa assay will be performed according to manufacturer instructions without supplementation of antithrombin.

Routine biochemistry (creatinine, urea, ASAT, ALAT, bilirubin, triglycerides, albumin) and inflammatory markers (CRP, procalcitonin) will be analysed using standard automated hospital laboratory systems. Platelet count will be obtained from standard automated haematology analysers.

Arterial blood gas analysis will provide calcium, haemoglobin, and hematocrit values at the time of sampling.

### Viscoelastic testing

2.7

Viscoelastic testing will be performed immediately on the ICU using the ClotPro® device. Testing will follow manufacturer-specific standard operating procedures. After electronic patient identification entry, the corresponding test channel and cartridge will be selected. Test-specific pipette tips will be scanned, and citrated whole blood will be transferred into the test cup, gently mixed, and the measurement initiated.

The following assays will be performed according to anticoagulant type:

LMWH / UFH: EX-, RVV-, RVH-, ECA-test.UFH: additional IN/HI-test.

Recorded parameters include CT, CFT, A5, A10, MCF, lysis time (LT), maximum lysis (ML), and alpha angle. Time from sampling to test initiation will be documented. After test completion, measurement channels will be prepared according to hygiene standards. Residual blood will be discarded in designated biohazard containers. The POC devices used in this study, which are operated outside the central laboratory, undergo weekly quality control in accordance with the manufacturer’s specifications.

### Thrombin generation

2.8

Thrombin generation will be measured using the Innovance® ETP assay (Siemens Healthineers, Marburg, Germany) on an automated coagulation analyser (BCS XP, Siemens Healthineers). Measurements will be performed in platelet-poor plasma. Coagulation will be initiated by addition of tissue factor and phospholipids in the presence of calcium according to manufacturer instructions. Thrombin formation will be quantified via cleavage of a chromogenic substrate, and the increase in optical signal over time will be recorded continuously. The assay software corrects for α2-macroglobulin–bound thrombin activity. From the resulting thrombin generation curve, the following parameters will be derived:

Endogenous thrombin potential (ETP; area under the curve)Peak thrombin generationLag time (time to initiation)Time to peak thrombin generation

Thrombin generation is included as a plasma-based global coagulation assay to complement whole-blood viscoelastic testing and Anti-Xa activity measurements. We acknowledge that PPP-based TGA differs from whole-blood clot dynamics and is sensitive to cellular effects; therefore, TGA results will be interpreted as a complementary plasma-based global readout rather than a direct proxy for whole-blood viscoelastic parameters.

